## Pilot studies: We conducted a prospective phase I study examining the safety of volume expansion for children admitted with clinical features of severe malaria (impairedconsciousness or deep breathing) complicated by acidosis (base excess <-8). Patients recruited to the study underwent continuous monitoring of blood pressure, pulse rate, respiratory rate, oxygen saturation and central venous pressure using a multichannel recorder. Fifty-three children were recruited and all had evidence of compensated shock on admission, with tachycardia, tachypnoea and prolonged capillary refill time (≥3s). Mean central venous pressure (CVP) [standard error] at admission was low: 2.9 [0.5] cm water (see Figure); in the group with severe acidosis (base excess<-15) 44% had hypotension (systolic blood pressure < 80 mmHg). Improvements of haemodynamic indices and a reduction in acidosis followed administration of either saline or albumin. By 8 hours the mean CVP had increased to 7.5 [0.5] cm water (F=34.4, P<.001) and was associated with a reduction in mean respiratory rate 49 [2] to 41 [1], F=7.0, P=.009, reduced tachycardia 151 [5] to 141 [3], F=3.4; P=.06 and reduced capillary refill time. No child developed evidence of the life threatening complications of pulmonary oedema and raised intracranial pressure. We concluded that both albumin and saline were safe and that doses of between 20-40mls/kg given over the first hour after admission resulted in a correction of the features of hypovolaemia and resolution of the acidosis9.

Figure: Central Venous Pressure measurement in children with malarial acidosis: correction of hypovolaemia with volume replacement

Central venous pressure (CVP) measures the pressure in the column of blood returning to the heart (preload). In health, this is normally 5-8cm H2O. In sick children higher preloads ~ 8-10cm are often required. In these children with severe malaria complicated by acidosis CVP was low at admission (0 hours) and normalised following 20-40mls/kg intravenous bolus of 0.9% saline or 4.5% albumin (indicated by the diamond).

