##### c. Sampling

1. **Sample size determination**

These are pilot studies designed primarily to examine the safety of Gelofusin in children with severe malaria complicated by acidosis. As Phase I studies they are designed to provide adequate data to justify progression to next phase ie: multicentre studies, but with the desire to avoid exposure of a large group of children to a therapeutic intervention for which there is no available data in severe malaria. The trial will therefore, provide important data on the volumes required of Gelofusin in achieving satisfactory improvements in haemodynamic features of shock such in a similar manner to that which has been previously observed in children given albumin9. Formal sample sizes will therefore not be calculated. We aim to recruit 80 children: 40 will have moderate acidosis and 40 will have severe acidosis. 20 children in each group will receive Gelofusin and 20 will receive albumin. Since we showed that the greatest benefit of albumin was in those with coma24, at least 50% of the children recruited will have coma. Gelofusin, would be used in preference to albumin in larger studies if mortality were 10% (confidence interval 7.5-12.5%) or less.

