**Randomisation procedure**

Randomisation will be conducted using a sealed card system. In the case of an emergency, where a child meets the clinical criteria for severe malaria but has evidence of profound shock (systolic blood pressure that is unrecordable or less < 80mm Hg) and volume resuscitation is required immediately, a children will be randomised before the receipt of the laboratory results and whilst consent is being obtained. The first 20mls/kg bolus will be given while the mother or guardian of the child is being consented and blood tests obtained.At this point if consent for the trial is refused or the malaria slide is negative for *P. falciparum* malaria parasites the child’s subsequent management will be as per local clinical protocol and by the attending clinicians’ judgement. The child will be dropped from the analysis of the study and the study number reallocated.

All children will be intensively monitored. The purpose of the intensive monitoring will be to establish the relative dose response and safety of each fluid regime required for correction of volume deficits and to monitor haemodynamic changes (in respiratory rate, oxygen saturation, heart rate, blood pressure and urine output) and clinical response induced by either colloid. To guide further management a central venous pressure line (CVP line) will be inserted into any child that develops refractory shock (failure to attain level one goals after one hour) or features suggestive of pulmonary oedema (development of bilateral fine, basal crepitations and falling oxygen saturations).

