**b) Provisions for data verification and validation.**

Currently all data is directly entered in File-Maker Pro where most variables entered have dichotomous values only and the values for numerical fields are selected from a list. Initial and final diagnoses are also chosen from a list of common diagnoses. The programmes have been written to include logical and range checks and flags for the reduction of duplication errors. Appropriate information quality control procedures are already established. Children fulfilling the admission criteria for the study will be flagged by the computer to alert the admitting physician.

Descriptive statistics will be used to compare the clinical characteristics of the groups at baseline (admission), 30minutes, 1 hr, 4 hrs, 8 hrs, 12 hrs and at 24 hours, by intervention. The major outcomes of interest will be the resolution of clinical features of shock and major side effects or complications; development of abnormal clotting indices, pulmonary oedema and death (as dependant variables) between the different interventions (independent variables). The primary measure of this outcome will compare the proportions attaining level one goals for resuscitation in those receiving albumin and Gelofusin. Using ANOVA baseline (admission) haemodynamic parameters (heart rate, respiratory rate, oxygen saturation, mean blood pressure and coma score) will compared to those at 1 hr, 2 hours and 8 hours between the different intervention groups. For the purpose of analysis percentage mean change in the parameter will be used between the baseline and next time point.

Expected outcome: We have shown that albumin results in low mortality (< 5%), whilst saline was associated with an overall mortality ~20%, rising to 46% in those with coma. Historical control data from children with the same clinical criteria show mortality was between 30-50%, when volume expansion was not routine. If the dose response to Gelofusin is similar to albumin then assessment of the clinical safety of Gelofusin will take the above mortality data into consideration, as well as the evidence arising from the coagulation studies.

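### The primary comparison is written by colloid only, although allocation is planned 20:20 within two acidosis groups; stratifying it by acidosis group would recover power at no cost

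*Protocol*

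**What the plan says.** **Design.** Section 8c (Sample size determination) gives the structure: "40 will have moderate acidosis and 40 will have severe acidosis. 20 children in each group will receive Gelofusin and 20 will receive albumin". The same paragraph states "Formal sample sizes will therefore not be calculated", so 80 is a recruitment target and not the result of a power calculation. Groups A and B are then described separately, with different planned volumes and infusion times.

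**Analysis.** Section 9b states the primary measure: "The primary measure of this outcome will compare the proportions attaining level one goals for resuscitation in those receiving albumin and Gelofusin". The same paragraph names the interventions as the independent variables and presents its descriptive statistics by intervention. Acidosis group does not appear in the analysis text. No test is named for the proportions.

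**Evidence that the groups differ.** Section 4 (Pilot studies) reports that "in the group with severe acidosis (base excess<-15) 44% had hypotension (systolic blood pressure < 80 mmHg"). Systolic pressure within the age threshold is one of the level one goals. Section 4 (Interpretation of the findings) describes moderate acidosis as the group with lower mortality.

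**Allocation.** The Randomisation procedure uses sealed cards and does not say that they are stratified. In an emergency "a children will be randomised before the receipt of the laboratory results and whilst consent is being obtained", so base excess, and hence the acidosis group, is not yet known.

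**The concern.** A design that fixes numbers within two prognostic groups is normally analysed by those groups. If the 40 children per arm are treated as one homogeneous sample, the difference in attainment between moderate and severe acidosis goes into the standard error, although the balanced allocation has already removed it from the treatment contrast. The test then rejects less often than its nominal 5% and is less able to show that one colloid resuscitates worse. With 40 per arm there is little power to spare, and the comparison informs whether Gelofusin goes forward to multicentre trials.

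A second, smaller issue arises if the 20:20 split is not achieved. An unstratified difference would then carry part of the difference in severity between the arms.

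**Working it through.** **Inputs from the protocol.** 2 groups × 2 colloids × 20 = 80 children, which agrees with the stated target. No alpha, power, effect size or attainment rate is stated, so there is no power figure to reproduce.

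**Assumptions.** Two-sided 5%; attainment on albumin (moderate/severe) from 80%/60% to 90%/40%; for power, a common odds ratio of 0.33 against Gelofusin, which gives Gelofusin rates of 57%/33%, 65%/25%, 75%/25% and 75%/18% for the four rows below. The unstratified two-proportion test is compared with the Cochran-Mantel-Haenszel (CMH) test stratified by acidosis group, both without continuity correction, by exact enumeration of the four binomial counts.

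**Why the unstratified test is conservative.** Write p1 and p2 for the attainment rates in the moderate and severe groups and p for their mean. With equal group sizes,

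p(1 − p) = ½[p1(1 − p1) + p2(1 − p2)] + [(p1 − p2)/2]².

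The last term does not belong in the error when allocation is balanced within groups. At 90%/40%: 0.2275 = 0.165 + 0.0625. The standard error used is √(2 × 0.2275/40) = 0.107, and the true one is √(2 × 0.165/40) = 0.091. The effective critical value is 1.96 × 0.1067/0.0908 = 2.30, which corresponds to a false-positive rate of about 2.1%. Exact enumeration gives 2.0%.

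**Planned 20:20 in each group**

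| Attainment, moderate/severe | False-positive rate, unstratified | False-positive rate, CMH | Power, unstratified | Power, CMH | Power lost (points) |
|---|---|---|---|---|---|
| 80%/60% | 4.3% | 4.9% | 64.4% | 64.9% | 0.5 |
| 85%/50% | 3.3% | 4.9% | 55.3% | 59.7% | 4.4 |
| 90%/50% | 2.8% | 4.9% | 45.8% | 55.3% | 9.6 |
| 90%/40% | 2.0% | 5.0% | 38.5% | 52.0% | 13.4 |

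(Losses are taken before rounding.) If the two groups respond alike (80% against 55% in both), power is 67.2% unstratified and 67.3% with CMH, so stratifying costs nothing.

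**If balance is lost.** Take 24 moderate and 16 severe children in one arm, the reverse in the other, and no true colloid effect. The spurious difference is (24 − 16)(p1 − p2)/40 = 0.2 × (p1 − p2).

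| Attainment, moderate/severe | Spurious difference (points) | False-positive rate, unstratified | False-positive rate, CMH |
|---|---|---|---|
| 80%/60% | 4 | 6.0% | 5.0% |
| 85%/50% | 7 | 8.1% | 5.0% |
| 90%/50% | 8 | 9.2% | 5.0% |
| 90%/40% | 10 | 11.1% | 4.9% |

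**How likely is that split?** Even if the cards were wholly unstratified, with 40 children per arm and 40 per group, the hypergeometric probability of 24:16 or worse in either direction is 11.7%. Averaged over all possible splits, the unstratified test's false-positive rate is 4.8% in each of the four scenarios. The distortion therefore applies conditionally, to a particular trial that happens to be imbalanced; it is not an inflation of the error rate over repeated trials.

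**The case against.** **The protocol does not say the test is pooled.** This is true. The primary-measure sentence names no test and does not exclude stratification, and an analysis plan that is not available here may specify it. What remains is that the protocol itself states the primary comparison and lists the interventions as the only independent variables, although the recruitment plan is built on the acidosis groups. Correcting a stated comparison is more than asking for a detail that belongs in an analysis plan.

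**No stated power is lost.** This is also true. A reader might infer that the trial was sized within the acidosis groups and that the analysis discards that sizing. The document does not support this, because it expressly declines a formal calculation. The comparison is also not the only randomised evidence on resuscitation: the volume of colloid needed is a primary endpoint, and haemodynamic parameters are compared by ANOVA.

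**The comparison is not biased.** A reader might infer that the emergency route confounds colloid with severity. It does not. Those children are still randomised, so any imbalance is a matter of chance, and under the planned 20:20 the bias is zero. The emergency route covers only children in profound shock, so imbalance arising from it alone should be rarer than the 11.7% above.

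**The gaps in attainment are assumed.** This objection stands. The 44% hypotension figure is measured before treatment and has no moderate-group comparator. Attainment is measured after treatment, with volumes adjusted to targets, which may narrow the gap. At 80%/60% the loss is negligible.

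**Conclusion.** The point holds as a free improvement of minor to moderate weight for a pilot. As written, the primary comparison omits the grouping on which allocation is planned. Analysed that way under 20:20, it is valid but conservative. The power lost runs from nothing, if the groups respond alike, to about 13 points at assumed attainment of 90% and 40%. These sizes depend on the assumed rates and on the common odds ratio of 0.33; the protocol supplies neither. No systematic bias is shown, and a distorted result would need a chance imbalance in acidosis group between the arms.

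**What to change.** In Section 9b, state that the proportions attaining level one goals will be compared between Gelofusin and albumin stratified by acidosis group (moderate, severe), using a Mantel-Haenszel risk difference with 95% CI and a CMH test, and that proportions will also be shown by acidosis group. Define the group from admission base excess for every child analysed, including those randomised by the emergency route.

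Do not extend the stratified large-sample test to death. At the protocol's expected albumin mortality of under 5%, no more than about 0.05 × 40 = 2 albumin deaths are expected, and the strata would be too sparse. Report deaths by arm and acidosis group with exact confidence intervals.

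The cost is a sentence or two in the analysis text. Base excess is already an eligibility measurement and blood gases are taken at admission, so no further children, samples or procedures are needed.

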## Design and results: We randomly assigned children with severe malaria and metabolic acidosis (base excess <-8) to treatment with either albumin or saline: patients with moderate acidosis (base excess between –8 and -15) received 20 ml/kg; and those with severe acidosis (base excess <-15) received 40 ml/kg. For ethical reasons, a control (maintenance only) group was only included for patients with moderate acidosis. 150 children were enrolled. There was no difference in the rate of resolution of acidosis between the groups; however, requirement for alternative treatments was significantly more common in the maintenance only control group (P =0.004). Overall, mortality was significantly lower in patients receiving albumin (2/56; 3.6%) than those treated with saline (11/61; 18%) (2= 6.1, P=0.01). The improved mortality was entirely confined to the children admitted in deep coma, where mortality was (1/21; 5%) in albumin recipients as compared with (11/24; 46%) in saline recipients (P =0.002). Only one child developed pulmonary oedema (in the saline group) (overall incidence <1%) and 10 (7%) of the 135 survivors had neurological sequelae. Prior to the study mortality in children with malaria and severe acidosis had been consistently documented at between 25-40%, hence the low rate in the albumin recipients (4%) is lower than any previously reported patients with similar severity of disease. Our finding that the beneficial effect of albumin was greatest in the comatose patients (5% in the albumin treated group) and that most of the deaths in the saline treated patients appeared to be neurological in origin, is consistent with the predicted physiological effects of albumin14.

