**Group A: Moderate acidosis**

Children will receive 20mls/kg of either Gelofusin or 4.5% human albumin solution. This will be given over the 30minutes following admission. However, the final volumes given will depend upon the attainment of pre-defined resuscitation targets (see later). Each intervention arm should contain at least 10 children in coma (Blantyre coma score ≤2).

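### The coma-score ANOVA has no term for coma at admission although children are recruited to a coma quota, so any arm difference among comatose children is diluted

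*Protocol*

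**What the plan says.** Section 9(b) of the protocol fixes the method, the contrast and the scale for coma score. The method is "Using ANOVA baseline (admission) haemodynamic parameters (heart rate, respiratory rate, oxygen saturation, mean blood pressure and coma score". The contrast is that these "will compared to those at 1 hr, 2 hours and 8 hours between the different intervention groups". The scale is given as "For the purpose of analysis percentage mean change in the parameter will be used between the baseline and next time point". Neither a factor for coma at admission nor a restriction to comatose children is stated.

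Section 8(c), on sample size, makes coma part of the recruitment plan: "at least 50% of the children recruited will have coma". The Group A text applies this to each arm, "Each intervention arm should contain at least 10 children in coma (Blantyre coma score ≤2", and Group B carries the same requirement. The inclusion criteria ask for impaired consciousness, deep breathing or both, plus acidosis, so a child can enter without being in coma. The reason for the quota is the earlier trial of albumin against saline, of which section 4 says: "The improved mortality was entirely confined to the children admitted in deep coma".

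**The concern.** The plan treats coma at admission as important enough to control at recruitment, but the analysis of coma score takes no account of it. A child with a Blantyre score of 2 or less can gain several points. A child admitted for deep breathing with near-normal consciousness can gain few or none. Two things follow when both kinds of child are compared by arm alone:

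- The large difference in change between the two kinds of child is counted as unexplained variation, although the quota keeps the arms similar in their mix.
- If the colloids differ only in comatose children, the average difference over everyone is a fraction of the difference in comatose children.

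Both push this comparison towards finding no difference. In a trial asking whether Gelofusin resembles albumin, such a result could be taken for similarity when the analysis had little chance of showing anything else. What is at stake is the information in one secondary neurological measure.

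**Working it through.** **1. The quota.** "We aim to recruit 80 children: 40 will have moderate acidosis and 40 will have severe acidosis" and "20 children in each group will receive Gelofusin and 20 will receive albumin". That is 2 acidosis groups × 2 arms × 20 = 80 children, 40 per arm. At least 10 comatose children in each of the 4 cells gives 4 × 10 = 40, which is the stated 50%. At the floor, each arm has 20 children in coma and 20 not.

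**2. Dilution.** Let f be the share in coma and δ the arm difference among comatose children, with no difference in the others. The pooled difference is f × δ. For δ = 1.0 point it is 0.5 at a 50% share and 0.75 at a 75% share.

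**3. Error term.** Without a coma factor, the variance within an arm is about

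f·s_c² + (1 − f)·s_n² + f(1 − f)·(m_c − m_n)²,

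where s and m are the SD and mean of change in comatose (c) and other (n) children. The protocol gives none of these, so they are assumed. With f = 0.5, s_c = 1.0, s_n = 0.5, m_c = 2.5 and m_n = 0.5, the variance is 0.5 + 0.125 + 1.0 = 1.625 (SD 1.27). The last term, the gap between the two kinds of child, supplies 1.0 of the 1.625.

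Power is about Φ(difference ÷ (SD × √(2/n)) − 1.96), with n per arm:

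- Comatose only, n = 20: 1.0 ÷ (1.0 × 0.316) = 3.16, so power is Φ(1.20) = 0.89.
- All children, no factor, n = 40: 0.5 ÷ (1.275 × 0.2236) = 1.75, so power is Φ(−0.21) = 0.42.
- All children, gap removed: the variance is 0.625 (SD 0.79), 0.5 ÷ (0.79 × 0.2236) = 2.83, and power is Φ(0.87) = 0.81. A main-effect factor leaves a residual of δ/4 = 0.25 per cell, which adds 0.0625 to the variance; power is then about 0.77.

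With s_c = 1.5 the first two figures are 0.56 and 0.28 to 0.32 (s_n from 1.0 down to 0.5).

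**4. Simulation on a bounded score.** Assumptions: scores limited to 0–5; baselines 1–2 in coma and 3–5 otherwise; mean change 1.5 in coma (before the arm difference) and 0.4 otherwise; SD of change 1.0 to 1.5 in coma and 0.6 otherwise; a 1.0-point difference in comatose children only; two-sided 5% test. Ranges run over the SD in coma, at a 50% coma share.

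| Scale | Comatose only | All, no factor | All, coma factor |
|---|---|---|---|
| Absolute change | 0.50–0.84 | 0.22–0.34 | 0.43–0.71 |
| Percentage change (the protocol's) | 0.37–0.63 | 0.19–0.28 | 0.36–0.62 |

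At a 75% coma share on the percentage scale, power is 0.52–0.80 in comatose children against 0.40–0.64 pooled.

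**5. Where the loss comes from.** At an SD of 1.3 the three absolute-change figures are 0.63, 0.26 and 0.53, so the factor recovers (0.53 − 0.26) ÷ (0.63 − 0.26) = 73% of the loss. On the percentage scale they are 0.46, 0.22 and 0.45, and the factor recovers 0.23 ÷ 0.24 = 96%. With no true difference, the pooled test without the factor rejects only about 1.5% to 1.8% of the time instead of 5%, as expected when the error variance is inflated.

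**6. The scale.** Percentage change cannot be computed from a baseline of 0, so the deepest comas would drop out. The same one-point gain counts as +100% from 1 to 2 and +25% from 4 to 5.

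**The case against.** The strongest reply is that a stratum factor in an ANOVA is a detail for a statistical analysis plan, and that section 9(b) neither states nor excludes a breakdown by coma. This stands in part. That the comparison runs over all children is the natural reading of text that names only the intervention groups, and a later plan could add the factor. But the protocol does name the method, contrast, times and scale for this variable, and what it names does not use its own coma quota. The percentage scale is written down, not left open.

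The second reply is that little depends on it. This stands. The primary measure is the proportion attaining level one goals, which do not include coma score. The criterion for taking Gelofusin into larger studies is mortality.

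A reader might also infer more than the documents support:

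- *That the quota was meant to power a coma-score test.* Section 8(c) says no formal sample size is calculated and ties the quota only to where albumin's benefit was greatest.
- *That albumin was shown to speed recovery from coma.* The benefit in section 4 was in mortality, against saline. This trial has no saline arm, and its aims do not mention coma recovery.
- *That coma score must leave the ANOVA for a recovery-time endpoint.* Most of the loss comes from the missing factor. Such an endpoint would also need a scoring schedule that the protocol does not give: section 8(d) schedules clinical assessments and neurological monitoring without naming the Blantyre score.

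**Conclusion.** The point holds as a fault of efficiency and scale in one secondary analysis. On the protocol's percentage scale, at the 50% floor, leaving out coma at admission cuts power from about 0.36–0.62 to 0.19–0.28 for a 1.0-point difference confined to comatose children. Restricting the test to comatose children gives nearly the same power as adding the factor. On absolute change, restriction does somewhat better than the factor.

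The sizes rest on assumptions that the protocol can neither confirm nor refute: the 0–5 range, the SDs and mean changes, the 1.0-point difference and no difference in non-comatose children. The 50% share is the lowest permitted, so the loss shrinks if more comatose children are recruited. The direction was the same at both coma shares and on both scales. Priority is minor to moderate: nothing here puts the trial's main conclusion at risk.

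**What to change.** For coma score only, amend section 9(b) in three ways:

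- Add coma at admission (Blantyre score 2 or less against above 2) as a factor in the ANOVA.
- Report the arm comparison within children in coma at admission, at the 1, 2 and 8 hour points already planned.
- Use absolute or ordinal change in place of percentage change for this variable.

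The cost is one more model term and one within-stratum table. No extra children, visits or measurements are needed. The within-coma estimate rests on fewer children, as few as 20 per arm, and should be shown with its confidence interval.

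### The supportive haemodynamic comparison uses percentage change without adjustment for baseline, which wastes precision and suits coma score badly

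*Protocol*

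**What the plan says.** The analysis text stands in the protocol, section 9(b). It names the test and the parameters: "Using ANOVA baseline (admission) haemodynamic parameters (heart rate, respiratory rate, oxygen saturation, mean blood pressure and coma score) will compared to those at 1 hr", with later comparisons at 2 and 8 hours, between the intervention groups. It then fixes the scale: "For the purpose of analysis percentage mean change in the parameter will be used between the baseline and next time point". It mentions no adjustment for the baseline value and does not say what happens when a baseline is zero. The same section makes a different quantity the primary measure, namely the proportion attaining level one goals in each arm.

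The design is set out in section 8(c): "We aim to recruit 80 children: 40 will have moderate acidosis and 40 will have severe acidosis", and "20 children in each group will receive Gelofusin and 20 will receive albumin". That gives 40 children per colloid. On coma, section 8(c) says that "at least 50% of the children recruited will have coma". Under Group A, and in the same terms under Group B, it adds "Each intervention arm should contain at least 10 children in coma (Blantyre coma score ≤2"). No lower limit on the score is given. The protocol states that no formal sample size was calculated, so it gives no power, significance level or target difference for this analysis.

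**The concern.** Two separate weaknesses follow from the chosen scale.

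**Continuous parameters.** Percentage change subtracts close to the whole baseline value from the follow-up value, however weakly the two are related. When the correlation is moderate, or the baseline varies more than the follow-up, this adds noise that a baseline-adjusted model removes. In a trial of 80 children that precision is worth having. The first null hypothesis (section 6) concerns the effect on physiological parameters of shock, and this ANOVA is the stated between-arm comparison of those parameters. A noisy comparison makes two colloids look alike more readily than they should.

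**Coma score.** This is a short ordered scale, and at least half the children start at 2 or below. Dividing by a baseline of 1 or 2 gives the same one-point recovery very different weights, in the children whom the sample-size section singles out as having shown the greatest benefit from albumin.

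**Working it through.** **No figure to reproduce.** The protocol gives no power or precision for this analysis, so the check compares the planned scale with the alternative.

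**Inputs from the protocol.**
- 40 children per arm, 20 per arm in each acidosis group (section 8(c)).
- Pilot heart rate, mean [SE]: 151 [5] at admission, 141 [3] at 8 hours, 53 children recruited (section 4, Pilot studies).
- Implied SDs, if all 53 were measured at both times: 5 × √53 = 36.4 and 3 × √53 = 21.8.
- The SEs are printed as whole numbers, so rounding alone allows 4.5 to 5.5 (SD 32.8 to 40.0) and 2.5 to 3.5 (SD 18.2 to 25.5). An equal-SD case of 22/22 is therefore also run.

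**Assumptions not in the protocol.** Correlation ρ between baseline and follow-up of 0.3 to 0.7; true difference between colloids of 5 or 12/min; two-sided α of 0.05.

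**Why precision is lost.** Let x be baseline and y follow-up. To first order, 100(y − x)/x behaves like y − (141/151)x = y − 0.93x, so it is close to absolute change. The coefficient that minimises variance, which ANCOVA estimates, is ρ × SD(y)/SD(x). At ρ = 0.5 this is 0.5 × 21.8/36.4 = 0.30 with the pilot SDs, and 0.50 with equal SDs. The plan subtracts too much of the baseline in both cases.

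**Hand check at ρ = 0.5, pilot SDs, absolute change against ANCOVA.**
- Variance of change: 36.4² + 21.8² − 2 × 0.5 × 36.4 × 21.8 = 1325 + 475 − 794 = 1007 (SD 31.7). SE of the arm difference: 31.7 × √(2/40) = 7.1.
- ANCOVA residual variance: 21.8² × (1 − 0.5²) = 356 (SD 18.9). SE: 18.9 × √(2/40) = 4.2.
- With equal SDs the variance ratio is (1 + ρ)/2: 65%, 75% and 85% at ρ = 0.3, 0.5 and 0.7.

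**Simulated power, 40 v 40, heart rate.** The 12/min rows place the difference in the direction of a lower rate.

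| True difference | SDs | ρ | Percentage change | ANCOVA |
|---|---|---|---|---|
| 12/min | 36/22 | 0.3 | 29% | 72% |
| 12/min | 36/22 | 0.5 | 37% | 80% |
| 12/min | 36/22 | 0.7 | 53% | 91% |
| 12/min | 22/22 | 0.3 | 55% | 73% |
| 12/min | 22/22 | 0.5 | 69% | 77% |
| 12/min | 22/22 | 0.7 | 90% | 93% |
| 5/min | 36/22 | 0.3–0.7 | 8–13% | 17–28% |
| 5/min | 22/22 | 0.3–0.7 | 14–27% | 17–30% |

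The power of percentage change also depends on direction. With the difference towards a higher rate and the pilot SDs it is lower, at most about 45% at ρ = 0.7, while ANCOVA is unchanged at about 92%. Monte Carlo error is about one percentage point (√(0.5 × 0.5/2000) = 1.1 points). Type I error was about 5% for both methods.

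Respiratory rate shows the same pattern. From 49 [2] to 41 [1] the implied SDs are 14.6 and 7.3. At ρ = 0.5 and a difference of 0.65 × 7.3 = 4.7/min, power is 38% against 90%.

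**Coma score.** The required minimum is 10 children × 2 arms × 2 acidosis groups = 40 of 80 with a score of 2 or less. A one-point gain is 100 × 1/1 = +100% from 1 and 100 × 1/2 = +50% from 2. From 0 there is no value. If 0 is a possible score and 5% of 40 comatose children have it (assumed), two are expected and the chance of at least one is 1 − 0.95⁴⁰ = 87%. At 10% the figures are four and 1 − 0.90⁴⁰ = 98.5%.

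**The case against.** The strongest reply is that little hangs on this analysis. The primary measure is the proportion attaining level one goals, and section 8(d) gives the primary endpoints as correction of shock and the volume of colloid needed. The rule for preferring Gelofusin in larger studies is a mortality figure. The trial is a pilot without a formal sample size. All of this stands, and it makes the point one about a supportive analysis.

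Several stronger readings are tempting and are not supported.

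- **Power of 37% against 80% as the size of the loss.** That rests on 12/min, which exceeds the whole pilot improvement of 151 − 141 = 10/min and is assumed between two active colloids. At 5/min neither method detects the difference reliably.
- **Percentage change as the least efficient option.** It performs about as well as absolute change: at 12/min and ρ = 0.5 with equal SDs, 69% against 67%; with the pilot SDs it is two to three points worse. Most of the loss comes from not adjusting for baseline.
- **A biased contrast.** Under randomisation the unadjusted comparison is unbiased on average, and the Type I error confirms this. Only a chance imbalance in a given sample is at issue.
- **A coma analysis that cannot be computed.** The protocol prints a score of 2 or less but never the scale's range, and it gives no count of children at 0. The scale might also be read as the change in a group mean, which stays defined. However, an ANOVA needs a value for each child, so the wording is at best ambiguous.
- **Neglect of the acidosis groups.** The protocol says only that ANOVA will be used. Factors in the model may properly be left to an analysis plan, so silence here is not an error.

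**Conclusion.** The point holds as a recommendation on a supportive analysis. The protocol itself fixes percentage change, so this is not a detail left open. ANCOVA had higher power in every scenario tabulated. The gain is large with the pilot-implied SDs (about 8–45%, or up to 53% depending on direction, against 18–92%). It is modest with equal SDs (about 14–87%, or up to 90%, against 18–92%), and about 3 points at ρ = 0.7 and 12/min. In further equal-SD runs it had vanished by ρ = 0.9. These sizes rest on assumed correlations and effects, and on SDs derived from rounded SEs with 53 children taken as measured at both times.

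The arbitrary weighting of coma score at 1 and 2 needs no assumption beyond calculating the change child by child. The undefined value at 0 depends on the scale including 0. Nothing here touches the primary measure or the validity of the planned test.

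**What to change.** In section 9(b), delete the sentence on percentage change and replace the ANOVA as follows.

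- **Heart rate, respiratory rate, oxygen saturation and mean blood pressure:** at each stated time point, compare the absolute value between arms by ANCOVA, with the baseline value and acidosis group (moderate or severe) as covariates. Report the adjusted difference with its 95% CI. Including acidosis group follows the design, which sets 20 children per arm in each group.
- **Coma score:** analyse it on its own ordinal scale, adjusted for the baseline score, and report deaths separately. Ranking death as the worst coma category would create a composite endpoint, which is debatable and not needed here.

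The cost is analysis wording and two residual degrees of freedom (80 − 2 = 78 becomes 80 − 4 = 76; critical t 1.991 becomes 1.992). No extra children or measurements are required, because the baseline values and acidosis group are already recorded.
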